#### Baseline Characteristics and Other Factors

Participants characteristics, such as age; sex; race; neurological level of SCI according to the International Standards for Neurological Classification of Spinal Cord Injury [21]; etiology of SCI, time since SCI; vital signs (temperature, blood pressure, pulse rate and saturation); other treatments for spasticity before inclusion; and comorbidity will be registered at baseline. Medication will be registered at baseline and during assessments at phases 1 and 2.

Other factors that will be registered during the study are possible complications and side effects of ITB, such as temporary liquor loss, infection, epilepsy [37,38], and drowsiness. Serious adverse events and Suspected Unexpected Serious Adverse Reactions will be registered according to applicable guidelines.

### Statistical Analysis

Because of the small sample size, it is expected that the continuous variables will not be parametrically distributed; therefore, they will be presented as median with IQR. Furthermore, due to the small sample size, pre- and postassessments during the first phase or the ITB trial phase will be compared with descriptive statistics and differences will not be formally tested. In addition, the measurements in the second phase after definitive implantation of the baclofen pump (3, 6, and 12 months after implantation) will be compared with descriptive statistics. Changes over time in the outcome measures within patients will be visually explored.

For categorical variables, we will present numbers and corresponding percentages. To compare pre- and postassessment during the first phase or the ITB trial, cross tabs will be made. Our primary analysis population is the intention-to-treat analysis. Considering the study design, we expect a few missing data. In case of missing data, we will use generalized estimation equations analysis (<20% missing data) or multiple imputations (>20% missing data).

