**Objective:**

We aim to establish the safety of cervical administration of ITB on pulmonary function and sleep-related disorders in adults with a cervical spinal cord injury with functional hindering spasticity. In addition, we aim to explore the effect of cervical ITB on the reduction of spasticity; participant satisfaction; and improvement at the level of function, activities, and participation.

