### Sample Size

No sample size calculation was performed for this pilot safety study. On the basis of a previous comparable study by Bensmail et al [3] with 11 participants, we decided to include the same number of participants. We expect that we need to screen and recruit 25 participants to retain 11 participants at the start of the phase 1 because of the safety criteria for inclusion (Figure 1).

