#### Primary Outcome Measures

The primary objective of the study is to establish whether cervical administration of ITB is a safe treatment for spasticity without deterioration of pulmonary function and possible increased risk or increased severity of SAS. Safety will be determined by use of a capillary blood gas sample and an OSAsense or CPAP screening before and during the first phase of the study. We will use P_c_CO_2_ and the AHI or ODI as safety markers.

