## Discussion

### Anticipated Findings

A literature review [9] on cervical ITB suggests improvement of UE spasticity and function, without causing more complications than thoracolumbar ITB. However, the data prevent definite conclusions. In 2024, a retrospective case series by Mossner et al [10] was performed in children with hypertonia, highlighting the safety and efficacy of using cervical ITB. They concluded that the cervical catheter tip location for ITB was safe, was effective in controlling tone, and should be considered for the treatment of hypertonia. Larger studies with longer follow-up were suggested to further determine upper-limit dosing safety, along with long-term functional benefits in these patients. This study will be the first study that will investigate whether cervical administration of ITB is safe in adults with SCI.

In addition to safety, efficacy will be exploratively assessed before phase 1 and at 3, 6, and 12 months after implantation of the ITB pump. The intermediate and long-term effects of cervical administration of ITB on respiratory muscles affecting pulmonary functions and SAS, as well as the effects of decreasing spasticity of the UE and LE on participants’ satisfaction, function, activities, and participation, will be assessed.

Besides the aforementioned direct effect of reduction of spasticity on UE function, reduction of spasticity may have an additional indirect benefit on UE function. At the end of conventional rehabilitation, UE reconstructive surgery is a well-documented and effective treatment in tetraplegia to improve arm or hand function [39]. Spasticity may adversely affect the outcome of this surgery and is mostly considered as a contraindication and must be treated first [40,41]. In case of generalized spasticity, cervical ITB may enable UE reconstructive surgery and thereby indirectly improve UE function.

When cervical ITB seems to be both safe and effective, it will change the usual care of this treatment. The catheter tip position should then be dependent on the localization of spasticity and treatment goals: tip at thoracolumbar level for functionally hindering spasticity of the LE muscles and tip at cervical level for functionally hindering spasticity of UE and LE muscles.

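### Eleven participants can give a first estimate of respiratory safety but cannot establish it, and the plan does not commit to the one figure that would express that estimate: the proportion who meet a respiratory stop reason

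*Protocol article*

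**What the plan says.** The aim appears twice in strong form. The Objective paragraph of the Abstract reads "We aim to establish the safety of cervical administration of ITB on pulmonary function and sleep-related disorders". Primary Outcome Measures reads "The primary objective of the study is to establish whether cervical administration of ITB is a safe treatment for spasticity" and names the measures: "We will use P_c_CO_2_ and the AHI or ODI as safety markers".

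On size, the Sample Size section states "No sample size calculation was performed for this pilot safety study". The number is copied from a previous comparable study: "We expect that we need to screen and recruit 25 participants to retain 11 participants at the start of the phase 1".

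On analysis, the Statistical Analysis section expects that "continuous variables will not be parametrically distributed; therefore, they will be presented as median with IQR". Phase 1 pre and post assessments "will be compared with descriptive statistics and differences will not be formally tested". The same section plans visual exploration of within-patient change, counts and percentages for categorical variables, phase 1 cross tabs, an intention-to-treat population, and GEE or multiple imputation for missing data.

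On harm, the section ITB Trial (Phase 1) lists five reasons to stop. Four are respiratory: one on PcCO2, two on the ODI (with and without complaints), and one on the AHI in CPAP users. The fifth is lack of effect on spasticity. Study Design provides the end-of-phase-1 assessment (T1) for participants whose trial infusion was both safe and effective.

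Limitations calls the safety aim clear and concedes a lack of power for efficacy only.

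**The concern.** The protocol treats respiratory harm as something that happens to an individual who crosses a limit. A median with IQR describes the middle of the group, so it does not measure harm in that sense. The figure that would answer the primary objective is the proportion of participants who meet a respiratory stop reason. The article does not commit to it, with or without an interval.

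Nothing else links 11 participants to a conclusion of safety: there is no precision target and no trial-level criterion. Because the stated limitation covers efficacy alone, a reader could take a clean result in 11 people as settling the safety question. That matters, since Anticipated Findings looks ahead to practice: "When cervical ITB seems to be both safe and effective, it will change the usual care of this treatment".

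**Working it through.** **1. The plan's own figure.** The 11 cannot be reproduced because no error rate, margin, effect or SD is given. The question is what 11 can show.

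**2. What median and IQR register at n = 11.** The upper quartile lies at about the 8th to 9th ordered value, depending on the definition, so ranks 10 and 11 do not enter it.

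- Illustration (assumed PcCO2 values, equally spaced from 4.8 to 5.8 kPa): under linear interpolation, Q1 / median / Q3 = 5.05 / 5.3 / 5.55.
- Raise the top two values to 8.0: still 5.05 / 5.3 / 5.55. The same invariance holds under all nine standard quantile definitions tried.
- Raise the top three: Q3 becomes 6.75, and it moves under eight of the nine definitions.
- Change scores, nine at 0 and two at +2.0: Q1, median and Q3 are all 0 under all nine definitions.

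**3. Who reaches T1.** Study Design gives T1 to participants with a safe and effective trial infusion. Someone stopped for a respiratory reason may have no T1 value. If T1 is the post assessment, that participant drops out of the comparison or is handled by GEE or multiple imputation, although the value is missing because of the harm. Daily blood gas and overnight oximetry values exist, but Statistical Analysis does not say that they serve as the post value.

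**4. What no events would show.** Exact upper limit for 0 of n: 1 − a^(1/n), where a is the tail probability. The 95% level is my assumption; the article gives none.

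- Two-sided: 1 − 0.025^(1/11) = 0.285.
- One-sided: 1 − 0.05^(1/11) = 0.238.
- Other methods: 3/11 = 0.273 (rule of three); Wilson 0.259.
- At the safety board's review after six participants: 1 − 0.025^(1/6) = 0.459.

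Chance of seeing no event in 11, (1 − p)^11:

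- true risk 10%: 0.9^11 = 0.314
- true risk 15%: 0.85^11 = 0.167
- true risk 20%: 0.8^11 = 0.086

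**5. What one or two events would show.** Clopper-Pearson 95% limits, with x events: lower = 2.5% point of Beta(x, 12 − x), upper = 97.5% point of Beta(x + 1, 11 − x).

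- 1/11 = 9.1% (0.2% to 41.3%)
- 2/11 = 18.2% (2.3% to 51.8%)

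**The case against.** A reader might infer that median with IQR is the primary safety summary, and that the trial could be declared safe while two of 11 participants (18%) hypoventilate unnoticed. The documents do not support that. Statistical Analysis describes how continuous variables in general are presented; it does not call this the primary summary or say that safety will be judged on a stable median. The same section plans within-patient plots, percentages and cross tabs. Each participant who meets a respiratory rule is stopped and that infusion is not counted as safe, reasons for stopping are recorded, and a board reviews safety after six participants. Harm in two people would be hidden in the median and IQR, but not necessarily in the trial. This stands.

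The blind spot also has a condition. For raw values it is complete only if the affected people already held the top two ranks. In the illustration, moving the two lowest values to 8.0 kPa shifts Q1 / median / Q3 to 5.25 / 5.5 / 5.75. That is a change, but only of 0.2 kPa, and all three stay below the 6.5 kPa limit. For change scores the blind spot is general; the article does not say which will be summarised.

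Two further replies carry some weight. Intervals and listings often belong in a full protocol or SAP, neither of which is shown, and the article rules out tests, not intervals. It also calls the study a pilot and is open about its size. Neither reply removes the mismatch within the article itself: a stated aim of establishing safety, harm defined per individual, a stated summary that does not measure it, and a limitation that omits safety.

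**Conclusion.** The point holds as one of claim and reporting. It should be corrected, but it does not invalidate the design. Eleven participants can give a first estimate of respiratory risk and cannot establish safety: with no events the data would be compatible with a risk of up to 28% (two-sided exact 95%) or 24% (one-sided). These limits assume that all 11 start infusion and are assessed, that participants are independent, and that 95% is the chosen level. The 28% is the upper end of what a clean result leaves open; it is not an expected risk.

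The planned plots and stopping rules may show affected individuals, but they do not yield a risk estimate. That T1 leaves out harmed participants is a possibility, because the article does not fix which measurement is the post value.

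A reader might also infer that the sentence on usual care must be removed. It is conditional and sits in the Discussion, so softening it is optional editing.

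**What to change.** - **Main safety result:** report the number of participants, out of all who start infusion, who meet any of the four existing respiratory stop reasons, with an exact 95% confidence interval. The stop reasons stay as written.
- **Individual data:** show each participant's baseline, worst on-infusion and last PcCO2 and AHI or ODI, whichever index applies. Drawing the worst value from the daily phase 1 measurements keeps participants without a T1 assessment in view.
- **Wording:** in the Abstract objective and in Primary Outcome Measures, replace establishing safety with a first or preliminary estimate of respiratory safety. In Limitations, say that the sample size limits the safety conclusion too, and that 0 of 11 would leave a risk of up to 28% open.

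The cost is one exact interval, one listing and some rewording, with no extra participants or measurements. The downside is a more modest claim and a visibly wide interval. The Results section says that no analysis had been done as of June 2025, so this could be fixed before analysis. Because six participants had already entered phase 1 in an open single-arm study, the change should be dated.

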## Methods

### Study Design

This multiphase single-arm intervention study will contain 2 phases. We will first start with screening and recruitment to determine if there is an indication for, and if it is safe to start treatment with ITB. Phase 1 will be the safety phase, in which an extracorporeal pump will be used to investigate whether cervically administered ITB leads to reduction of spasticity without adverse effect on pulmonary function and sleep-related disorders. In case of a safe and positive test, we will continue to the next phase (phase 2) in which a baclofen pump is implanted. After implantation, the dosage of ITB will be slowly increased to the optimal setting, and if the participant uses oral spasmolytics, these are phased out. The optimal setting varies in accordance with patient conditions. In this phase of the study, we will focus, in addition to pulmonary function and sleep-related disorders, on the reduction of spasticity; improvement of participants’ level of function, activities, and participation; and participant satisfaction according to the International Classification of Functioning [11].

All participants will be assessed once before the start of phase 1 (T0A1), at the start of phase 1 (T0A2), and daily during phase 1 (T0B). In the case of a safe and positive test, participants will be assessed at the end of phase 1 (T1). During phase 2, they will be assessed at 3, 6, and 12 months (T2, T3, and T4) after baclofen pump implantation. We chose to start the assessment in phase 2 only after 3 months following the implantation because in the first 3 months, the pump settings will still be regularly adjusted to optimize the daily dosage of ITB.

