Daily capillary blood gas samples will be taken, and continuous pulse oximetry during sleep, by use of the OSAsense, will be recorded. If the participant is set on a continuous positive airway pressure (CPAP) device, the CPAP device is read out. The trial will be determined as unsafe and will be stopped if the P_c_CO_2_ is >6.5 kPa for 2 days in a row, according to hypoventilation rules in adults as mentioned by Berry et al [28]. The trial will also be stopped when participants without SAS, during the trial, will develop complaints matching SAS and the Oxygen Desaturation Index (ODI) is between 5 and 15 [27]. The ODI represents the number of desaturations per hour.

A third reason to stop the trial is when participants during the trial have no complaints matching SAS, but the ODI is >15 [27]. If the participant uses a CPAP device, the setting of the device may be adjusted to stay within the safety margin. This safety margin is set at an AHI <5 [24]. This adjustment will be registered. A fourth reason to stop the study is when, after adjustments of the CPAP device, it is not possible to stay within this safety margin [24]. A fifth reason to stop the study is if there is no effect on spasticity at the maximum dose of ITB (200 µg per day).

If the participant experiences a positive effect of the ITB on their spasticity, with a score between 1 and 3 on the Patient Global Impression of Change (PGIC) [29] without deterioration on functionality (PGIC 5-7) and there is not a clinically relevant deterioration of pulmonary function or SAS, it is considered a safe and positive ITB trial with an indication for intracorporeal pump implantation (phase 2) and treatment with ITB at cervical level. We opted for these cut-off values for assessment of reduction of spasticity according to the algorithm established by the European working group for spasticity in adults [30].

If, during the trial, no effect is observed on spasticity or there is a clinically relevant deterioration of pulmonary function or SAS, the trial will be discontinued. This is considered a negative test in which there is no indication for treatment of spasticity with ITB. The catheter and the subcutaneous infusion port will then be removed (Figure 2)*.*

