## Results

The study has started in January 2021. Funding was completed in March 2022. The first participant was enrolled in May 2023. As of June 2025, we have enrolled 6 patients in phase 1 and 3 patients in phase 2. No data analysis has been done yet. We expect data collection to be completed and published in 2028.

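### The missing-data rule (GEE below 20% missing, multiple imputation above) does not fit a purely descriptive analysis of about 11 people, and it leaves open how never-implanted participants are handled at 3, 6 and 12 months

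*Protocol article*

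**What the plan says.** All references are to the protocol article.

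- **Missing data (Statistical Analysis).** One rule covers every outcome: "In case of missing data, we will use generalized estimation equations analysis (<20% missing data) or multiple imputations (>20% missing data". It follows the remark "Considering the study design, we expect a few missing data".
- **Population (Statistical Analysis).** "Our primary analysis population is the intention-to-treat analysis". No separate set is named for phase 2.
- **Analysis (Statistical Analysis).** Continuous variables are given as median with IQR and categorical variables as counts and percentages. Phase 1 before-and-after comparisons are descriptive and untested, phase 2 is also descriptive, and within-person change is explored visually.
- **Entry to phase 2 (Study Design).** "In case of a safe and positive test, we will continue to the next phase (phase 2) in which a baclofen pump is implanted". T2, T3 and T4 are timed at 3, 6 and 12 months after implantation.
- **After a negative or unsafe test (ITB Trial, Phase 1).** "The catheter and the subcutaneous infusion port will then be removed".
- **Size (Sample Size).** "No sample size calculation was performed for this pilot safety study"; "We expect that we need to screen and recruit 25 participants to retain 11 participants at the start of the phase 1".

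**The concern.** There are two separate problems.

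**The rule does not match the analysis it is meant to protect.** A missing-data method serves an estimate from a stated model. Here the outputs are medians, quartiles, cross tabs and plots, and no regression or marginal model is specified. GEE is itself an analysis model: it uses the values that are present and, unweighted, in general needs the rest to be missing completely at random. It is not an alternative to multiple imputation on a scale set by the amount missing. The choice depends on why values are absent and what is being estimated, not on whether a percentage falls above or below 20.

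**The rule does not separate a missed visit from an outcome that cannot exist.** Someone whose catheter is removed after phase 1 has no post-implantation visit. That absence follows from carbon dioxide, sleep-apnoea or spasticity results in phase 1, so it is informative. If these people stay in an intention-to-treat denominator for T2-T4 and the upper branch applies, their phase 2 values would be drawn from participants who passed the test they failed. The exploratory 3-, 6- and 12-month results would then describe people who never had a pump, probably too favourably.

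**Working it through.** **Inputs.** 11 participants starting phase 1 (Sample Size). The 20% threshold and the single population (Statistical Analysis). Implantation only after a safe and positive test (Study Design). Assessment schedule (Table 1). The article gives no expected non-implantation rate, so a range is assumed in step 3. The figure of 11 was taken from an earlier study and not calculated, so there is no planned calculation to reproduce.

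**1. Per-participant count.** Share absent at T2-T4 if k of 11 are not implanted = k/11:

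| k | k/11 | Branch |
|---|---|---|
| 1 | 9.1% | GEE |
| 2 | 18.2% | GEE |
| 3 | 27.3% | multiple imputation |
| 4 | 36.4% | multiple imputation |

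One more person not implanted switches the method. If T2-T4 are described only in implanted participants, non-implantation contributes 0% and the threshold depends on missed visits alone.

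**2. Effect of the unstated denominator.** Take the same three non-implanted people.

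- By participant: 3/11 = 27.3%, above the threshold.
- By value, for grip strength (screening, T2, T3, T4): (3 × 3)/(11 × 4) = 9/44 = 20.5%, just above.
- By value, for spirometry (six scheduled occasions in Table 1): (3 × 3)/(11 × 6) = 9/66 = 13.6%, below. Study Design also makes T1 conditional on a safe and positive test. If T1 is counted as absent too, the share is 12/66 = 18.2%, still below.

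The same three people fall on either side of the threshold depending on how the percentage is counted. Exactly 20%, which arises for example at 1 of 5 or 2 of 10 implanted participants, has no assigned method.

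**3. How easily 3 of 11 is reached.** With an assumed non-implantation probability p,

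P(X ≥ 3) = 1 − (1−p)^11 − 11p(1−p)^10 − 55p²(1−p)^9.

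- p = 0.1: 1 − 0.314 − 0.384 − 0.213 = 0.09
- p = 0.2: 1 − 0.086 − 0.236 − 0.295 = 0.38
- p = 0.3: 1 − 0.020 − 0.093 − 0.200 = 0.69

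**4. What the two methods do at this size.** Both were simulated with normal data, no true effect and an assumed within-person correlation of 0.5.

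- *GEE*, four visits, exchangeable working correlation, 600 runs, nominal 95% interval. With 11 people and complete data, coverage was 0.90 with ordinary sandwich errors and 0.95 with bias-reduced errors and a t reference on n − 1 degrees of freedom. With 15% missing at random the figures were 0.91 and 0.96. With 6 people they were 0.86 and 0.96.
- *Multiple imputation*, one baseline predictor, 50 imputations, 1000 runs, 11 people, values missing completely at random. Coverage was 0.98 with 3, 5 or 6 missing. Median interval width was 1.85, 2.66 and 3.52 SD, against 1.63, 1.95 and 2.31 SD from the observed cases alone.

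Both methods can be made to run. In this setting imputation gave wider intervals than the observed data.

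**The case against.** The strongest reply is that the article nowhere says it will impute phase 2 values for people without a pump, and much of its wording points the other way. T2-T4 are counted from implantation, phase 2 data are described as post-implantation measurements, and a failed test is classified as a result. The authors plan for phase 1 failures and still expect few missing data, which suggests they had missed visits in mind. This stands: a reader might infer that outcomes will be invented for people who were harmed or did not respond, but the documents do not state that. They only fail to exclude it.

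The primary question is also answered elsewhere. Primary Outcome Measures determines safety from capillary carbon dioxide and the AHI or ODI before and during phase 1. Complications and reasons for stopping are recorded, and a safety board reviews the first six participants to complete phase 1. This stands too, so a claim that the rule hides the primary safety risk is not supported.

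Nor does the text support a claim that neither method can work with 11 people. Small-sample corrections bring GEE coverage to about 0.95, and simple imputation covers at 0.98. Test error rates would be beside the point, because no tests are planned.

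Finally, "we have enrolled 6 patients in phase 1 and 3 patients in phase 2" is an enrolment count. Some of the six may still be in phase 1 or awaiting a pump, so it is not a failure rate of one half.

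Phase-specific analysis sets may be defined in a full protocol or analysis plan that is not shown. That would close the second problem but not the first, because the rule printed in the article is itself unsuitable.

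**Conclusion.** The point holds as a wrongly fixed rule with an open ambiguity. GEE and multiple imputation serve no analysis in this plan, the share missing is not a valid switch between them, and the switch is undefined in its denominator and at exactly 20%. These conclusions follow from the text and need no assumption.

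The second part is conditional. If the intention-to-treat set is carried into phase 2 and missingness is counted per participant, 3 of 11 not implanted (27.3%) is enough to bring in imputation from those who passed. The chance of reaching 3 is 0.09 to 0.69 for assumed non-implantation rates of 10% to 30%. The exposure is limited to the exploratory phase 2 results. The simulation figures depend on the assumed correlation and on normal data; they show only that imputation gained nothing over observed data in that setting.

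**What to change.** Delete the GEE and multiple-imputation sentence and state that no values are imputed. In its place, say:

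- Phase 1 outcomes are reported in all participants in whom catheter placement or infusion was started.
- T2-T4 outcomes are reported as observed in implanted participants, with n at each visit and individual profiles.
- The number not implanted, explanted or withdrawn is reported with reasons, out of all who started phase 1.

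The cost is a few sentences and less analysis work. The downside is a smaller n at the later visits. The Results section says no data have yet been analysed, so the change can be made before any result is known.

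If the sponsor wants to keep a model for some outcome, the text should name the outcome, the quantity estimated, the population, the assumed reason for missing values and the small-sample correction.

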### Study Procedures

#### Screening and Recruitment

Before participants are included in the study, they will be assessed by an experienced SCI rehabilitation physician to check the indication for treatment of their spasticity by ITB. If there is an indication, participants will be screened for the presence of SAS by the use of OSAsense (OSAsense BV) [24]. The OSAsense consists of a validated online questionnaire and a nightly saturation and pulse rate measurement (pulse oximetry). The OSAsense algorithm, based on the questionnaire and pulse oximetry, is able to detect SAS with a sensitivity of 100%, a specificity of 35%, a negative predictive value of 100%, and a positive predictive value of 79.4% [25]. If, according to the algorithm, there is any suspicion of SAS, polysomnography will be performed, and the patient will be set up for SAS treatment if necessary. In addition, a morning capillary blood gas sample will be taken to determine the P_c_CO_2_. We chose to take a capillary blood gas sample because there is a strong correlation between samples collected from the fingertip capillaries and the arterial blood samples in relation to the analysis of blood [26].

These measurements determine the safety for participants to start the first phase of the study. The start of the first phase of the study will be determined as safe if the participant is stable enough to undergo surgery (defined by neurosurgeon), capillary blood gas shows a P_c_CO_2_ between 4.5 and 6.5 kPa, and there are no symptoms of SAS or, in the case of SAS, the participant is adequately set to SAS treatment with an Apnea-Hypopnea Index (AHI) <5. These cut-off values have been chosen according to the applicable guidelines in the Netherlands [27].

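### The phase 1 missing-data rule makes no exception for participants stopped by design; if T1 is the post value for PcCO2, their observed rises are left out or replaced by modelled values

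*Protocol article*

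**What the plan says.** The primary objective is to show a "safe treatment for spasticity without deterioration of pulmonary function" and without new or worse sleep apnea. PcCO2 is a named safety marker, together with AHI or ODI (Primary Outcome Measures). Safety is to be judged from a blood gas sample and "an OSAsense or CPAP screening before and during the first phase of the study".

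Four parts of the protocol article bear on the analysis:

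- **Statistical Analysis, comparison:** "pre- and postassessments during the first phase or the ITB trial phase will be compared with descriptive statistics", with no formal test. The visit that counts as post is not named. The primary population is intention-to-treat.
- **Statistical Analysis, missing data:** "In case of missing data, we will use generalized estimation equations analysis (<20% missing data) or multiple imputations (>20% missing data"). No separate rule is given for participants stopped in phase 1.
- **Study Design:** "In the case of a safe and positive test, participants will be assessed at the end of phase 1 (T1"). A participant whose test is unsafe or without effect has no T1.
- **ITB Trial (Phase 1):** blood gas is sampled daily. "The trial will be determined as unsafe and will be stopped if the P_c_CO_2_ is >6.5 kPa for 2 days in a row". Implantation also requires that "there is not a clinically relevant deterioration of pulmonary function or SAS"; no PcCO2 change is attached to that clause.

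At entry, PcCO2 must lie "between 4.5 and 6.5 kPa, and there are no symptoms of SAS" or these are adequately treated (Screening and Recruitment).

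**The concern.** T1 is both conditional on safety and a candidate for the post value in a safety comparison. If it is used, the T0A2-to-T1 change in PcCO2 is seen only in participants whose test was already called safe and positive. Those stopped for high PcCO2 have no T1 because of the outcome being summarised.

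The written missing-data rule then reaches exactly these people. GEE in its usual form, run on the observed pre and T1 values, assumes that the gap is unrelated to the unseen outcome. Multiple imputation would supply a T1 value for an infusion that was halted as unsafe, and it is hard to say what such a number means. Neither is needed, because these participants have real daily values up to the stop.

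At stake is the description of a primary safety marker in 11 people, where one or two large rises may be the main message.

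**Working it through.** **1. Which visit can be post?** Phase 1 rows of Table 1 for the primary outcomes:

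| Measure | T0A2 (before) | T0B (during) | T1 (end) |
|---|---|---|---|
| Capillary blood gas | yes | yes, daily | yes |
| Pulse oximetry | no | yes | no |
| Spirometry | yes | only if dyspnea | yes |

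No single visit serves all three. Oximetry can only use T0B, and scheduled spirometry can only use T1. For blood gas both are open, so the choice of post matters most for PcCO2.

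**2. Where the missing-data rule would send them.** The 11 at the start of phase 1 come from Sample Size. The article does not define the 20% denominator; participants without T1, out of 11, is an assumption here.

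- 1/11 = 9% and 2/11 = 18%: GEE.
- 3/11 = 27% and above: multiple imputation.

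Lack of effect also means no T1. If a share p of participants ends phase 1 without T1 for any reason, the binomial chance of 3 or more out of 11 is 9%, 38%, 69% and 88% for assumed p of 10%, 20%, 30% and 40%.

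**3. Why the stopping rule does not replace a summary of change.** The limit equals the upper entry bound. From an entry value of 4.5 kPa, a rise of 6.5 - 4.5 = 2.0 kPa stays within it. From 6.4 kPa, a rise just above 6.5 - 6.4 = 0.1 kPa on two consecutive days crosses it. That is proper behaviour for an individual stop, but it means that change from baseline has to be shown separately.

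**4. Illustrative size.** The article gives no PcCO2 distribution and no trial length, so every input is assumed: entry mean 5.3 or 5.6 kPa, SD 0.4, cut to 4.5-6.5; true rise with mean 0.3 (SD 0.3) or 0.5 (SD 0.5), building linearly over 4 days; daily SD 0.2 to 0.4; stops for PcCO2 only. Results over simulated trials of 11:

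- Number meeting the limit: 0.20 to 1.84 on average.
- Mean last on-infusion rise: 0.60 to 1.16 kPa in those stopped, 0.27 to 0.45 in the rest.
- Median rise in all versus not stopped: 0.30 versus 0.29 (entry 5.3, rise 0.3, daily SD 0.3); 0.49 versus 0.40 (entry 5.6, rise 0.5, daily SD 0.3). The widest gap is 0.50 versus 0.39 (daily SD 0.4). The range of the gap is 0.01 to 0.11 kPa.

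A harsher set (entry mean 5.0 to 5.6, mean rise 0.3 to 1.0 with SD 0.5 to 0.8, 5 days, daily SD 0.2, stop rate 5% to 43%) gives gaps of 0.03 to 0.32 kPa. The top of that range needs a mean rise of 1.0 kPa and 43% stopped.

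**The case against.** The strongest reply is that the article never says post is T1. It judges safety before and during phase 1, and oximetry is not taken at T1, so reading both safety markers at T0B makes the plan coherent. On that reading the selection problem for PcCO2 disappears. This stands, and it is why the point is conditional. A reader might infer that the plan definitely drops or imputes stopped participants; the text does not support that.

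Second, naming the post visit is often left to the analysis plan, which is not shown. That is fair, and the unnamed visit alone would be no finding. The article does, however, commit to a missing-data rule beside an intention-to-treat population, and that rule fits badly with a visit that stopped participants cannot have. It can be argued that T1 is not scheduled for them rather than missing. That is reasonable, but the rule does not say so.

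Third, omission or an empty imputation is not inevitable. A GEE that includes the T0B series keeps the stopped participants, and imputation that conditions on T0B need not breach missing-at-random, since the stop follows from observed values. Both points stand. What remains is the meaning of a T1 value after a halted infusion.

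Fourth, stopped participants are not invisible: their test is classed as negative, within-patient courses are to be explored visually, and the data safety monitoring board reviews safety after 6 participants complete phase 1. This limits the harm but does not settle the numerical summary.

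Two further inferences should be resisted. The 6.5 kPa limit is not an error, and the article does not offer it as a measure of change. Nor does the June 2025 count (6 enrolled in phase 1, 3 in phase 2) show that participants lack T1. If the 3 are among the 6, between 0 and 3 of 6 might, but no reason is given and some may still be in phase 1 or awaiting a pump.

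**Conclusion.** The point holds in conditional form. The missing-data rule makes no exception for phase 1 stops, T1 exists only after a safe and positive test, and the post value is open between T0B and T1. If T1 is used for PcCO2, the summary either covers only those judged safe or contains modelled values for halted infusions.

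The shift in the median is probably small, 0.01 to 0.11 kPa in the main illustration, and that figure rests wholly on assumed inputs. It exceeds this range only under the larger rises and stop rates of the harsher set. The real cost is that the largest observed rises, which are the safety signal, could be missing from the numerical summary. If T0B is intended, one sentence closes the matter. This is a cheap improvement rather than a flaw that threatens the trial.

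**What to change.** Keep the stopping rule as it is. In the analysis section, state that:

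1. For every participant who starts infusion, within-person PcCO2 change from T0A2 is summarised from observed T0B values: the last on-infusion value, and the maximum rise shown with the number of days sampled.
2. T1 and later values are not imputed for participants stopped in phase 1.
3. Each stop is listed with its reason beside that participant's T0A2 value.

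The cost is wording only: all samples are already scheduled, and the article reports that no data had been analysed as of June 2025. The downside is that a maximum over more days rises by chance alone, so it must be read together with the last on-infusion value.
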